## Abstract

**Background:**

Prolonged weaning from invasive mechanical ventilation is a major challenge in critically ill patients failing a spontaneous breathing trial. Levosimendan, a calcium sensitiser, has been shown to improve respiratory muscle function. However, its effect on clinically relevant endpoints in difficult to wean patients has not yet been investigated. We aim to assess whether levosimendan shortens the weaning process in invasively ventilated intensive care unit (ICU) patients who fail a separation attempt. The objective is to assess the effect of levosimendan on the number of ventilator-free days and alive at day 28.

**Methods:**

The WEANing with LEvoSimendan Study (WEANLESS) is an investigator-initiated, multicentre, double-blind, parallel-group, randomised clinical superiority trial. Adult invasively ventilated patients who failed a separation attempt are randomly assigned to receive either intravenous levosimendan (intervention) or placebo (control). The primary outcome is the number of ventilator-free days and alive at day 28 from randomisation. WEANLESS also evaluates the effects of levosimendan on patient-reported outcomes, measured through daily dyspnoea scores and uses an EQ-5D-5L questionnaire. Additionally, we will evaluate healthcare resource utilisation and intensive care capacity, assessed through reintubation rates, ICU readmissions within 90 days, the need for non-invasive respiratory support and ICU length of stay. WEANLESS includes a pharmacokinetic analysis of levosimendan and its metabolites.

**Discussion:**

WEANLESS is the first clinical study that is sufficiently powered to determine the effect of intravenous levosimendan in difficult to wean patients on the duration of weaning from invasive ventilation.

**Ethics and dissemination:**

WEANLESS is registered before the inclusion of the first patient at clinicaltrials.gov; the study protocol has been approved by the relevant ethics committee. Its findings will be disseminated through presentations at scientific conferences and publications in a peer-reviewed journal.

**Trial registration number:**

NCT07105202.

STRENGTHS AND LIMITATIONS OF THIS STUDYUse of a clinically meaningful and well-defined primary endpoint: ventilator free days and alive (VFD) up to day 28, this composite measure captures both liberation from ventilation and survival, reflecting the goals of intensive care unit (ICU) care.With VFD as a composite endpoint, it is not possible to distinguish between patients who die early (who automatically receive a score of 0) and patients who are never successfully extubated within 28 days.This study has a multicentre, double-blind design, which enhances both internal validity and external generalisability across diverse ICU settings.

## Introduction

### Background

 Acute respiratory failure is a life-threatening condition that may develop in the course of many diseases, including pneumonia, sepsis, trauma, chronic lung diseases or after surgery. Especially the elderly, patients with comorbidities and immunocompromised patients are at risk of developing acute respiratory failure. In these patients, invasive ventilation is a lifesaving intervention. However, invasive ventilation is a double-edged sword. While being lifesaving, invasive ventilation is associated with serious complications which are directly related to the duration of the ventilation. Successful liberation of patients from invasive ventilation (‘weaning’), represents a crucial step in the recovery process following severe lung failure. Unfortunately weaning can be a complicated process. A prolonged weaning duration worsens patient outcomes, increases the risk of death and extends the length of stay in the intensive care unit (ICU).^1^ Duration of invasive ventilation is among the strongest predictors of 1 year functional outcome.^2^ In addition, weaning duration impacts healthcare resource utilisation. Costs of ICU are very high, in the Netherlands ±3000 euro per day and critical care resources are limited. Therefore, reducing duration of ventilator weaning affects direct financial healthcare costs and the opportunity for other patients of consumption of finite critical care capacity. In conclusion, early ventilator weaning is important for the benefit of the individual patient, but also for societal benefit.

ICU acquired weakness of the respiratory muscles plays a significant role in weaning from invasive ventilation.^3^ A disbalance in the load imposed on the respiratory muscles and capacity of the respiratory muscles results in ventilator weaning failure. In patients ventilated >24 hours, 63% developed respiratory muscle weakness at the time of weaning.^3^ No medical intervention has been shown effective in improving respiratory muscle function in ICU patients. This is surprising given that respiratory muscle weakness frequently develops in ventilated patients and is associated with adverse outcome. Therefore, interventions that improve respiratory muscle function in patients difficult to wean from invasive ventilation are much needed. The calcium sensitiser levosimendan has shown positive effects on the respiratory muscles in experimental models, healthy subjects and ventilated ICU patients.^4^,^6^ The effects on weaning outcome are unknown.

### Clinical trial rationale

Respiratory muscle weakness frequently develops in invasively ventilated patients and is strongly associated with adverse clinical outcome.^3 7^ Respiratory muscle weakness in ventilated patients is partly explained by muscle atrophy,^8^ but also by impaired force generation at a given intracellular calcium concentration, that is, a so-called reduced calcium sensitivity of contraction.^9^ Reduced calcium sensitivity reduces contractile efficiency, that is, more energy is needed and more CO_2_ is generated as compared with non-ICU patients. Levosimendan is a cardiac inotrope that improves calcium sensitivity of force generation of cardiac muscle and is approved for treatment of acute heart failure. Regarding the diaphragm, research followed a stepwise approach to investigate the effects of levosimendan on diaphragm function, progressively moving from basic to clinical studies. First, levosimendan improved the calcium sensitivity of force generation in diaphragm fibres.^4^ This was the very first study to demonstrate that pharmacological modulation of the troponin complex improves human diaphragm function. Second, in a double-blind placebo-controlled trial in healthy subjects, levosimendan improved in vivo contractile efficiency of the diaphragm by 21%.^5^ Levosimendan also restored diaphragm contractility after loaded breathing (reversal of muscle fatigue). Third, in a double-blind placebo-controlled study, we demonstrated that levosimendan increased tidal volume, minute ventilation and decreased arterial CO_2_ in critically ill ventilated patients.^6^ No serious adverse events occurred. In summary, previous work demonstrated that respiratory muscles of invasively ventilated patients show impaired calcium sensitivity of contraction and that levosimendan improves calcium sensitivity. Given these results, we hypothesise that levosimendan shortens the weaning process by enhancing respiratory muscle function, ultimately leading to a reduced ICU length of stay and lower mortality rates compared with standard care.

### Objectives

The primary objective of WEANing with LEvoSimendan Study (WEANLESS) is to determine the effect of intravenous levosimendan on the number of ventilator free days and alive (VFD) at day 28 after randomisation. This is a composite endpoint combining both mortality and the duration of ventilation. A patient who dies before day 28 will be assigned 0 VFD. Day 0 will be defined as the day of randomisation.

Secondary objectives include evaluating the effects of levosimendan on patient-reported outcomes, measured through daily dyspnoea scores and quality of life measured with the the EuroQol five-dimensional (EQ-5D-5L) questionnaire. The study will also investigate its impact on healthcare resource utilisation and intensive care capacity, assessed through reintubation rates, ICU readmission within 90 days, the need for non-invasive respiratory support, ICU length of stay and mortality. Furthermore, the pharmacokinetics of levosimendan and its metabolites will be analysed in a subset of study patients, with measurements taken up to 120 hours after infusion of the medication.

### Trial design

The WEANLESS is an investigator-initiated, multicentre, double-blind, parallel-group, randomised clinical superiority trial with a 1:1 allocation ratio. Participants will be randomised to receive either intravenous levosimendan or placebo. The study is registered in a publicly accessible clinical trial database.

## Methods: participants, interventions and outcomes

### Patient and public involvement

Before drafting the protocol, consultations were held with patient representatives from the Netherlands Patients Federation, Lung Foundation Netherlands and FCIC. Invasively ventilated patients often describe dyspnoea as one of the most distressing experiences in the ICU.^10^ It is a major contributor to ICU-related post-traumatic stress disorder and reduced quality of life.^11 12^ Given its significant impact, dyspnoea has been identified as a key secondary endpoint in this trial.

### Study setting

The trial will be conducted in the ICUs of participating (academic and top-clinical) hospitals in the Netherlands. A current list of participating centres can be found on https://clinicaltrials.gov/.

#### Population

WEANLESS will include patients aged over 18 years, admitted to participating ICU, ventilated for more than 48 hours and who have at least one failed separation attempt, defined as a failed spontaneous breathing trial (SBT, see SBT failure criteria) or a failed extubation (reintubation within 7 days) (‘difficult to wean from invasive ventilation’).

### Eligibility criteria

Patients are eligible for participation in WEANLESS if: (1) admitted to a participating ICU; (2) aged 18 years or older; (3) invasively ventilated for more than 48 hours and (4) have at least one failed separation attempt (a failed SBT or failed extubation). The following exclusion criteria have been defined: pre-existing neuromuscular disease, endotracheally intubated primarily for neurological reason, treatment with intermittent haemodialysis, treatment limitation decision in place: do not reintubate, previous treatment with levosimendan within 30 days, currently in another interventional trial or contraindications for levosimendan. Contraindications for levosimendan are: severe renal failure (creatinine clearance <30 mL/min) unless managed with continuous appropriate kidney replacement therapy (such as continuous veno-venous haemofiltration (CVVH)), severe liver failure (Child-Pugh class C), history of torsade des pointes; known significant mechanical obstructions affecting ventricular filling/outflow or both; prolonged QTc interval (QTc >470 ms); pregnancy, breast feeding; known hypersensitivity to levosimendan. See figure 1 for the enrolment procedure.

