### Interventions

#### Explanation for the choice of comparators

Patients who meet all the inclusion criteria and none of the exclusion criteria will be randomised to receive either the intervention (intravenous levosimendan) or placebo, in addition to standard care for weaning from mechanical ventilation. A placebo was selected as comparator because no active comparator exists for this indication.

The placebo group, like the intervention group, will receive standard ICU care for weaning from mechanical ventilation. To ensure comparability between groups and uniformity across study sites, the weaning process will be standardised using predefined criteria for initiating and assessing SBTs and extubation.

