#### Placebo

The placebo group will receive intravenous multivitamins (Soluvit N) as a placebo. When diluted (10 mL in 500 mL glucose 5%), Soluvit N provides a yellow colour that matches the characteristic appearance of levosimendan. This is consistent with practices in other intervention trials with levosimendan,^22^,^25^ LevoHeartShock (NCT04020263). The route, volume and infusion rate are matched with the administration of levosimendan to maintain blinding during the study.

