### Assignment of interventions: allocation

#### Sequence generation

Clinical research platform Castor Electronic Data Capture (https://www.castoredc.com/) will be used to perform the randomisation and is Good Clinical Practice. Participants will be randomised in a 1:1 allocation ratio to ensure equal distribution between the intervention and control groups. To minimise potential site-specific effects, stratified randomisation by study centre will be applied.

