### Assignment of interventions: blinding

#### Who will be blinded

This study will follow a double-blind design, meaning that both participants and all investigators involved in recruitment and outcome assessment will remain blinded to treatment assignments at all times.

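### The hypersensitivity exclusion covers levosimendan only, although the control arm is infused with a named multivitamin product

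*Protocol article*

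**What the plan says.** The Eligibility criteria section introduces its exclusions with "The following exclusion criteria have been defined" and then lists them; it does not present them as examples. The list ends with "currently in another interventional trial or contraindications for levosimendan", and those contraindications are then spelled out, some with numerical limits. The only allergy item among them is "known hypersensitivity to levosimendan". The other product-related item, recent previous treatment, also concerns levosimendan.

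The Placebo section states: "The placebo group will receive intravenous multivitamins (Soluvit N) as a placebo". The product is diluted in glucose 5% and was chosen because its yellow colour resembles levosimendan. It adds: "The route, volume and infusion rate are matched with the administration of levosimendan to maintain blinding during the study".

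The rule for entry is in the section explaining the choice of comparators: "Patients who meet all the inclusion criteria and none of the exclusion criteria will be randomised". Sequence generation sets the ratio: "Participants will be randomised in a 1:1 allocation ratio". On blinding, the article says that "both participants and all investigators involved in recruitment and outcome assessment will remain blinded to treatment assignments at all times", and the Discussion extends this to treating clinicians. The Levosimendan section under Intervention description allows weekly repeats, up to four doses in all.

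**The concern.** The plan accepts that a known hypersensitivity to an infused product is a reason not to enrol a patient, but applies that principle to one of its two products. Every enrolled patient may receive either product, and the recruiting investigators do not know which. The criterion therefore has to be met for both products before randomisation.

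At stake is an avoidable exposure for the occasional patient whose record already shows a reaction to the control product. A written criterion matters more here than in many trials. The patients are invasively ventilated, and the Informed consent section expects consent to come frequently from a legal representative, so the patient may be unable to mention an allergy.

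**Working it through.** The point is about eligibility and disputes no figure in the plan. It is checked by following the stated rules for one hypothetical patient, and then by bounding the size.

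**Following the rules**

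1. Take an adult in a participating ICU, ventilated for more than 48 hours, with a failed separation attempt and a recorded reaction to Soluvit N. All four inclusion criteria are met.
2. Go through the exclusions. None refers to Soluvit N, to its components or to the control infusion. The hypersensitivity item refers to levosimendan. No exclusion is met.
3. The entry rule then allows randomisation.
4. With 1:1 allocation, the probability of assignment to Soluvit N is 1/(1 + 1) = 0.5.
5. If so assigned, the patient receives between one and four infusions. Four is a ceiling, because dosing stops at successful weaning.
6. The section on discontinuing or modifying the intervention names heart rate, mean arterial pressure and patient request, with a general allowance to stop if necessary. Emergency unblinding is available for severe events. Both act after exposure has begun.

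The diluent, glucose 5%, is common to both arms, so the gap concerns the multivitamin product itself.

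**Size**

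The Sample size section gives 125 patients per group. Its 117 per group before the allowance for non-normality reproduces from a difference of 3.9 days and an SD of 10.6 (116 by the normal approximation, 116.9 by the t-test, hence 117). Nothing in this point changes those figures.

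Let p be the proportion of otherwise eligible patients with a known reaction to the product. The documents do not give p, so the values below are assumptions chosen only to show the range. The expected number of such patients in the control arm is 125 × p. As a deliberately extreme case, suppose each of them falls from the assumed mean of 15.6 ventilator-free days to 0. The control mean then moves by 15.6 × p.

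| Assumed p | Expected in control arm (125 × p) | Shift in control mean (15.6 × p), days | Share of the 3.9-day target |
|---|---|---|---|
| 0.0001 | 0.0125 | 0.00156 | 0.04% |
| 0.001 | 0.125 | 0.0156 | 0.4% |
| 0.01 | 1.25 | 0.156 | 4% |

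For a safety outcome such as hypotension, the control-arm proportion could rise by at most p, which is 1 percentage point in the last row. Even there, and even if every affected patient had the event, the comparison of the arms would hardly move.

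**The case against.** The strongest objection is that the article condenses a longer protocol that is not shown. Precautions for the control product could stand there, in the enrolment diagram, or in the pharmacy and nursing procedures. In addition, nothing in the Eligibility criteria section is false, and it does not contradict the Placebo section. This stands as a limit: the full protocol may already have the criterion. It does not remove the point, because the article does not leave hypersensitivity to another document. It states the criterion, in a list presented as the defined one, and draws it too narrowly for the two products it describes.

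A second objection is that the documents give no contraindication, component list or reaction rate for Soluvit N. That also stands, and it is why no frequency is claimed. The point needs only the plan's own principle that a known reaction to an infused product is a reason for exclusion.

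Three stronger readings are tempting, and the documents do not support them:

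- A reader might infer that all 125 control patients are at risk. The gap concerns only eligible patients with an already known reaction, about half of whom would be assigned to the product.
- A reader might infer that control-arm reactions would make levosimendan look safer. That would need enough affected patients to move a comparison of 125 with 125. No figure in the documents suggests this, and the range above argues against it.
- A reader might infer that nobody could prevent the exposure once the patient is randomised. The Implementation section describes an unblinded team, mainly pharmacy staff, who know the allocation and supply the product. Screening or bedside staff could also notice a recorded allergy to a product that the article names openly. These are chances to catch the problem; the article assigns none of these people that check.

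**Conclusion.** The point holds as a narrow one. The stated exclusion list, followed exactly, admits a patient with a known reaction to the control product and gives that patient a 1 in 2 chance of being assigned to it, with up to four infusions. The number affected is not given and is presumably very small. The consequence is individual patient safety only; power, the primary analysis and the safety comparison are not materially affected.

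This rests on two assumptions: that the list in the article is the list used at screening, and that known reactions to the product are rare among eligible patients. If the first is wrong because the full protocol is wider, what remains is an inaccurate eligibility section in the article.

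**What to change.** Reconcile the Eligibility criteria section with the Placebo section so that the hypersensitivity criterion covers both study products and their components, and have it checked from the allergy record before randomisation. If the full protocol already contains such a criterion, correct the article's eligibility section to match it.

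The cost is a few words in the criteria, one line on the screening form and very few patients lost to recruitment. The sample size and the analysis stay as they are.

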**Figure 1 F1:**
[figure not shown]
Flow diagram for enrolment of a WEANLESS participant.

### Informed consent

If a patient is deemed potentially eligible, a member of the study team may approach the patient or their proxy even before the patient undergoes a separation attempt to provide information and obtain consent. Only if the patient subsequently fails the separation attempt, the study will proceed with randomisation and administration of the study medication. In cases where the patient or proxy has not yet been informed at the time of the failed separation attempt, the study team will initiate the informed consent process as soon as possible after separation failure. A window of up to 24 hours after a failed separation attempt is allowed to obtain informed consent. Given the critical condition of ICU patients, deferred consent procedures will frequently be applied by obtaining consent from a legal representative. If and when the patient regains decision-making capacity, informed consent will be asked from the patient. The patient information form is provided in the supplementary material.

### Additional consent provisions for collection and use of participant data and biological specimens

Separate consent will be obtained for the collection, storage and future use of data and biological samples for research beyond the primary study objectives. This will be addressed in a dedicated section of the consent form.

### Interventions

#### Explanation for the choice of comparators

Patients who meet all the inclusion criteria and none of the exclusion criteria will be randomised to receive either the intervention (intravenous levosimendan) or placebo, in addition to standard care for weaning from mechanical ventilation. A placebo was selected as comparator because no active comparator exists for this indication.

The placebo group, like the intervention group, will receive standard ICU care for weaning from mechanical ventilation. To ensure comparability between groups and uniformity across study sites, the weaning process will be standardised using predefined criteria for initiating and assessing SBTs and extubation.

#### Weaning process

To standardise the weaning process across all study sites, physicians are required to assess daily whether patients meet the criteria for an SBT. The criteria align with the weaning protocol developed by the Dutch Society of Intensive Care,^13^ which is supported by recent literature.^14^,^16^ We strongly encourage physicians to adhere to the criteria outlined below.

Criteria for initiating an SBT:

Adequate oxygenation: oxygen saturation (SpO_2_) >90% with fraction of inspired oxygen (FiO_2_) ≤50% and positive end expiratory pressure (PEEP) ≤8 cmH_2_O.Adequate respiratory rate: respiratory rate ≤34/min.Stable cardiovascular status: systolic blood pressure 90–160 mm Hg without or with minimal vasopressor use, heart rate ≤140/min.

When a patient meets all of the above criteria, an SBT will be performed. This trial should last at least 30 min and can be conducted using one of the following methods:

Using the T-piece.Pressure support mode, with pressure support (PS) ≤8 cmH_2_O and PEEP ≤7 cmH_2_O.Continuous positive airway pressure (CPAP) mode, with PEEP ≤7 cmH_2_O.

